### Randomization and blinding

The allocation sequence is computer-generated by an independent statistician using block randomization (block size = 3) with a 1:1:1 ratio for the MAG, ACU, and SHM group. Allocation concealment is implemented using sequentially numbered, opaque, sealed envelopes. Each envelope contained an allocation card corresponding to the group assignment. Envelopes will be opened sequentially by treating physicians to deliver the allocated intervention.

Given the nature of the magnetic stimulation, acupuncture, and sham magnetic stimulation intervention therapies, it is not possible for the treating physicians to be blinded in this trial. However, participants, outcome assessors, and data analysts will be blinded to group allocation. To minimize bias, strict separation of roles is maintained between intervention operators, outcome assessors, and statisticians throughout the trial. Blinding assessment will be conducted after the final treatment session. All participants will be asked to guess their group allocation from four options: PC6 MAG, PC6 ACU, PC6 SHM, or uncertain. These responses will be used to calculate the James Blinding Index, which quantifies blinding success on a scale from 0 to 1, where 1 indicates complete blinding (all “do not know”), 0 indicates complete unblinding (all correct), and 0.5 represents random guessing (29). Given the potentially perceptible differences between active magnetic stimulation and sham stimulation, a higher risk of functional unblinding may exist between the MAG and SHM groups, which will be considered when interpreting the blinding assessment results.

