## Method and analysis

### Research design

The present study is a three-arm RCT. Eligible PSCI patients will be enrolled from the Inpatient Department and Outpatient Clinic of Rehabilitation Medicine, West China Hospital, Sichuan University. Participants will be randomized in a 1:1:1 ratio to three groups: PC6 Magnetic Stimulation (MAG), PC6 Acupuncture (ACU), and Sham Magnetic Stimulation at PC6 (SHM). All three groups will concurrently receive rTMS (targeting the L-DLPFC). The study flowchart is presented in Figure 1, and assessment time points are detailed in Table 1. Ethical approval was granted by the Ethics Committee of West China Hospital of Sichuan University on March 13, 2024 (Approval No.: 20240313). The trial is registered at the Chinese Clinical Trial Registry: https://www.chictr.org.cn/, Registration No.: ChiCTR2400090768.

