### Sample size

This study employes a three-arm, parallel-group, randomized controlled design (1:1:1 allocation), with the MoCA score as the primary endpoint. One-way analysis of variance (ANOVA) is used to compare differences among the three groups. Due to the lack of a clear anticipated effect size, based on previous rTMS studies in PSCI (26–28), we adopt Cohen’s f ≈ 0.32 as the expected effect size. Using G*Power 3.1 (test type: one-way ANOVA; effect size *f* = 0.32; *α* = 0.05, two-tailed; power = 0.80), the estimated total sample size is 99 (33 per group) to detect significant differences in MoCA scores. To account for a potential 10% attrition rate, the final recruitment target is set at 105 participants (35 per group). Because *a priori* information on within-subject correlation and covariate R^2^ was unavailable, we used one-way ANOVA for conservative planning. The primary analysis will use longitudinal models with covariate adjustment, which is expected to provide equal or greater efficiency than the planning model.

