## Limitations

This single-center exploratory trial has several limitations. Firstly, although the L-DLPFC was selected as the target region, target localization was implemented via cap-based approaches (the “5-cm rule”) rather than neuronavigation techniques. Previous studies have demonstrated the imprecision of the “5-cm rule” for rTMS stereotactic localization, with evidence showing that this method may result in stimulation over non-prefrontal regions in a substantial proportion of subjects (64–66). This cap-based approach may therefore induce inter-individual localization variability and potentially compromise the internal validity of the trial. Secondly, clinical heterogeneity in PSCI may still influence treatment response. While key factors such as stroke subtype, lesion characteristics, and time from stroke onset to enrollment will be documented and explored as covariates in multivariable and sensitivity analyses, the trial may be not powered for definitive subgroup analyses. Thirdly, the use of a single acupoint (PC6, Neiguan) enhanced the rigor of experimental control, yet it deviates from routine clinical practice where multi-acupoint acupuncture is the standard modality. Thus, extrapolation of the study results to real-world settings should be performed with caution. Fourthly, despite efforts to optimize masking, blinding may be imperfect due to the distinct somatosensory experiences between acupuncture and magnetic stimulation, which may introduce expectation-related bias. Finally, the follow-up duration is relatively short, which limits conclusions regarding the long-term durability of cognitive and network-level changes; larger multicenter trials with longer follow-up will be necessary to confirm sustained clinical benefits.

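### A fixed, published block size of 3 lets anyone who has seen the earlier allocations deduce every third one, which weakens allocation concealment

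*Protocol article*

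**What the plan says.** All of the following is in the protocol article.

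- **Sequence** (Randomization and blinding): an independent statistician generates it by computer, "using block randomization (block size = 3) with a 1:1:1 ratio for the MAG, ACU, and SHM group". One block size is given. Neither varying sizes nor stratification is described.
- **Concealment** (same section): "Allocation concealment is implemented using sequentially numbered, opaque, sealed envelopes".
- **Who opens the envelopes** (same section): "Envelopes will be opened sequentially by treating physicians to deliver the allocated intervention".
- **Their blinding** (same section): "it is not possible for the treating physicians to be blinded in this trial".
- **Role separation** (same section): "strict separation of roles is maintained between intervention operators, outcome assessors, and statisticians throughout the trial". Staff who screen, consent or enrol are not among the roles listed.
- **Setting**: patients come from the inpatient and outpatient services of one rehabilitation department (Research design), and Limitations calls the trial single-centre.
- **Size** (Sample size): 105 participants, 35 per arm.

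**The concern.** With three arms at 1:1:1, a block of 3 is the smallest possible, and each block is one MAG, one ACU and one SHM in random order. Opaque envelopes hide the next card but not what follows from the cards already opened. The block size is printed in the article, there is one list at one centre, and those who open the envelopes know what they deliver.

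The risk is selection at entry. Someone who can foresee the next arm could, knowingly or not, change which patient is approached or when. The eligibility criteria leave room for this: ages 30 to 75, MoCA below 26 with no stated floor, and no stated window since stroke, so candidates may differ widely in expected recovery. Blinded assessment acts after allocation and does not address this. The planned regression adjusts for age, sex, education, time from onset, rehabilitation dose and lesion side. That could offset selection on those factors in part, but not on motivation or a clinician's impression of prognosis. The Discussion attributes differences between arms to the PC6 intervention, and that attribution depends on the next allocation being unforeseeable at enrolment.

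**Working it through.** **Inputs.** Block size 3 and ratio 1:1:1 (Randomization and blinding); 105 to be randomised, 35 per arm (Sample size). The article gives no figure for predictability, so there is none to reproduce. The inputs agree with each other: 105 / 3 = 35 complete blocks, which gives 35 per arm.

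**Assumption.** The guesser has seen all earlier allocations, knows the block size, and names the arm with most cards left in the current block.

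**Block of 3, by slot**

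| Slot | Arms still possible | Chance of a correct guess | Allocations |
|---|---|---|---|
| First | 3 | 1/3 | 35 |
| Second | 2 | 1/2 | 35 |
| Third | 1 | 1 | 35 |

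- Certain in advance: 35/105 = 33.3%.
- At least one arm ruled out: 70/105 = 66.7%.
- Best-guess success: (1/3 + 1/2 + 1)/3 = 61.1%, or 64.2 of 105 expected correct. Unpredictable allocation gives 1/3, or 35 of 105.

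**Larger fixed blocks, size known to the guesser.** With b cards per block, m = b/3 per arm, an allocation is certain when all cards left are of one arm. The expected number of certain slots per block is 1 + (m−1)/(b−1) + (m−1)(m−2)/[(b−1)(b−2)] + …

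- b = 6: 1 + 1/5 = 1.200; 1.200/6 = 20.0%.
- b = 9: 1 + 1/4 + 1/28 = 1.286; 1.286/9 = 14.3%.
- b = 12: 1 + 3/11 + 6/110 + 6/990 = 1.333; 1.333/12 = 11.1%.

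Exact enumeration of expected correct guesses per block gives the second measure:

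| Block size | Certain in advance | Expected correct per block | Best-guess success |
|---|---|---|---|
| 3 | 33.3% | 1.833 | 61.1% |
| 6 | 20.0% | 3.367 | 56.1% |
| 9 | 14.3% | 4.787 | 53.2% |
| 12 | 11.1% | 6.144 | 51.2% |

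**Randomly varying blocks.** In a simulation (500 runs) of sizes 6 and 9, the guesser knew the set of sizes but not their order. About 5.5 of 105 allocations were certain and about 57 of 105 guesses (54%) were correct. The mixture 6, 9 and 12 was not simulated.

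The two measures respond differently. Larger or varying blocks remove most of the certain allocations, but they lower best-guess success only modestly, and it stays well above 33%.

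**The case against.** The strongest case against the point is that foreknowledge does no harm unless the person who has it also controls entry. Opening an envelope to deliver treatment is a step after enrolment, and the article never says that treating physicians screen, consent or enrol. It also speaks of physicians in the plural and of two acupuncturists, so no single person need see the whole sequence. A condensed article may leave enrolment roles to the full protocol.

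Much of this stands, and it limits the claim. A reader might infer that concealment is wholly defeated. The documents do not support that: the first slot of each block stays at 1/3, the second at 1/2, and the envelopes and the independent list still protect what cannot be deduced. A reader might also infer that selection bias is occurring, or that one physician follows every allocation. Neither is stated. Shared knowledge within one department is plausible, but it is an assumption.

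The objection does not remove the point itself. The block size is a stated design value, not an omitted detail, and the deduction follows from it by arithmetic. Nothing in the article keeps past allocations from those who enrol.

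**Conclusion.** The point holds as a weakness of concealment. With the published block of 3, 35 of 105 allocations are certain in advance and another 35 are narrowed to two arms. Best-guess success is 61% against 33%. These figures are exact for someone who has seen the earlier allocations.

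Bias in the treatment comparison is conditional: it requires that such a person can influence who is enrolled or when. The documents neither establish nor exclude this, and they give no basis for putting a size on the resulting bias in MoCA change. If it occurred, assessor blinding and the planned covariates could not fully remove it. Confidence is high in the predictability and lower in actual harm. The change is worth making because it is cheap and because selection at entry cannot be undone later.

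**What to change.** **For allocations not yet made**

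1. The independent statistician reissues the remaining list and envelopes with randomly varying larger blocks in multiples of 3 (for example 6, 9 and 12). The sizes are not disclosed to the site or published while recruitment is open.
2. Each envelope is opened only after consent, eligibility and baseline MoCA are recorded and the envelope number is logged against the patient.
3. Enrolment decisions rest with existing staff who do not see past allocations, and enrolment is added to the stated role separation.

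Steps 2 and 3 matter as much as step 1, because block size alone leaves best-guess success above 50%.

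**For allocations already made**

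The documents do not show how many these are. Report who enrolled patients and whether they knew earlier allocations. Compare baseline characteristics between arms by position in block; selection would show as arm differences in third slots that are absent in first slots. With 35 patients per position at most, or about 12 per arm (35/3 = 11.7), this check is descriptive, and finding no imbalance would not prove that there was no selection.

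**Cost.** One reissue of the list and envelopes, a log entry per patient, and final arm sizes that may differ by a few patients because the last block may be incomplete.

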#### Group-specific interventions

##### MAG group

Patients will receive peripheral magnetic stimulation at the PC6 acupoint(Figure 2A). A figure-of-eight coil (outer diameter: 114.8 mm, inner diameter: 79.6 mm) will be used to deliver peripheral magnetic stimulation. The stimulation frequency will be 20 Hz (high frequency), with intensity gradually increased from 80% RMT until slight flexion of the index and middle fingers is observed. The total stimulation duration per session will be 24 min.

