##### ACU group

Patients will receive manual acupuncture at the PC6 acupoint (Figure 2B). All acupuncture procedures will be performed by the same two acupuncturists with over 6 years of clinical experience, who have completed clinical operational training organized by the research team. Following routine disinfection of the local skin at the acupoint, sterile disposable stainless-steel filiform needles (0.25 mm × 40 mm) will be inserted. And lifting-thrusting and twirling techniques will be applied to achieve deqi. Needle manipulation will be performed once every 10 min to maintain needle sensation, with a total of two manipulations, and the needles will be retained for 30 min.

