##### SHM group

Patients will receive sham peripheral magnetic stimulation at the PC6 acupoint (Figure 2C). A figure-of-eight coil will be used, with the stimulation frequency set to 0 Hz and intensity set to 0. The coil will be positioned with its non-active (reverse) side facing the skin to ensure that no magnetic field is delivered to the median nerve. However, the auditory output of the device will be identical to that of the active stimulation to maintain blinding (34). The stimulation procedure, including coil placement, duration, and pulse protocol structure, will be identical to that used in the MAG group.

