This study also incorporates numerous methodological considerations aimed at enhancing the quality of evidence and the reliability of result interpretation. First, we employed a three-arm randomized controlled design, where all participants received conventional high-frequency rTMS targeting the L-DLPFC, with additional PC6 intervention introduced as a variable. This design ensures ethical compliance while attributing intergroup differences to the specific effects of either magnetic stimulation or acupuncture at PC6. Since rTMS has been demonstrated to have therapeutic benefits for PSCI (56, 57), we avoided exposing the control group to entirely ineffective treatments, thereby safeguarding patient welfare. However, it is important to acknowledge that this approach may reduce the significance of intergroup differences. To address this, we ensured sufficient statistical power through rigorous sample size estimation and balanced enrollment criteria. Second, regarding blinding procedures, we implemented both assessor and patient blinding to the greatest extent possible. Although acupuncture and magnetic stimulation differ in somatosensory perception, the sham stimulation group used a simulated coil placed over PC6 without delivering pulses, making it difficult for participants to discern whether they received actual magnetic stimulation. All clinical assessments were conducted by independent evaluators unaware of group assignments to minimize subjective bias.

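### Participant blinding is stated without exception, but needle and coil arms cannot be masked from each other, so two of the three pairwise contrasts are open to participants

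*Protocol article*

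**What the plan says.** The section Randomization and blinding concedes that treating physicians cannot be blinded and continues: "However, participants, outcome assessors, and data analysts will be blinded to group allocation". No arm is exempted. The only pair for which it names a problem is the two coil arms, where "a higher risk of functional unblinding may exist between the MAG and SHM groups". Participants will guess their allocation after the last session (MAG, ACU, SHM or uncertain), and the guesses feed a James blinding index.

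The three procedures are described under Group-specific interventions:
- **ACU:** "sterile disposable stainless-steel filiform needles (0.25 mm × 40 mm) will be inserted". The needle is manipulated to obtain deqi and left in place for 30 minutes.
- **MAG:** a figure-of-eight coil for 24 minutes, "with intensity gradually increased from 80% RMT until slight flexion of the index and middle fingers is observed".
- **SHM:** "A figure-of-eight coil will be used, with the stimulation frequency set to 0 Hz and intensity set to 0". The coil is reversed, and sound and procedure are matched to MAG.

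The Discussion says the design permits "attributing intergroup differences to the specific effects of either magnetic stimulation or acupuncture at PC6". Limitations concedes that "blinding may be imperfect due to the distinct somatosensory experiences between acupuncture and magnetic stimulation" and that expectation-related bias may follow.

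**The concern.** A patient who has a needle inserted and manipulated in the forearm knows that it is not a coil. A patient under a coil knows that it is not a needle. The only sham in the trial imitates the coil. Participant blinding is therefore claimed for the whole trial, while the design can attempt it for one pair of arms only.

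What is at stake is the interpretation of the ACU contrasts. Comparing magnetic stimulation with acupuncture is a stated aim in the Discussion, and ACU is one of the three groups in the one-way ANOVA under Sample size. A difference between ACU and a coil arm would mix any effect of needling with the patient's expectation of a visibly different procedure, with different operators (two designated acupuncturists) and with a different session length (30 against 24 minutes). Such a difference cannot be read as a specific effect of acupuncture at PC6. A reader who relies on the blinding section alone would look for unblinding in the one pair that has a matched sham, and not in the two pairs that have none.

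**Working it through.** **Step 1. What each pair of arms allows.** Three arms give 3 × 2 / 2 = 3 pairwise contrasts.

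| Contrast | Procedures seen by the patient | Matching sham described | Role in the plan |
|---|---|---|---|
| MAG-SHM | coil and coil | yes (reversed coil, matched sound) | lead aim in the Discussion; fits the hypothesis in the Introduction |
| MAG-ACU | coil and needle | no | stated aim in the Discussion |
| ACU-SHM | needle and coil | no | part of the three-group test under Sample size |

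Two of the three contrasts set a needle against a coil. No sham needle, double dummy or screening of the forearm is described for any arm.

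**Step 2. The statements side by side.** Randomization and blinding treats participant blinding as a property of the trial. Limitations treats it as something that might fall short. The intervention descriptions make it impossible for two contrasts. The Discussion's sentence on specific effects names acupuncture alongside magnetic stimulation, and its reassurance about masking concerns the sham coil only. These statements cannot all stand.

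**Step 3. What the planned index would show.** The article gives three anchors for the James index: 1 (all do not know), 0.5 (random guessing) and 0 (all correct). It does not give the formula or weights, so I assume equal weight for every wrong guess:

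BI = [1 + P_DK + (1 − P_DK) × K] / 2, with K = (P_o − P_e) / P_e,

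where P_DK is the share answering uncertain, P_o the observed share of wrong guesses among the rest, and P_e the share of wrong guesses expected from the margins.

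The article's anchors are reproduced for three arms of 35:
- All uncertain: P_DK = 1, so BI = (1 + 1)/2 = 1.
- Random guessing: P_o = P_e = 2/3, K = 0, BI = 0.5.
- All correct: P_o = 0, K = −1, BI = 0.

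Now assume that nobody answers uncertain, that all 35 ACU patients guess correctly, and that coil patients choose only between MAG and SHM, with a share c correct in each coil arm. All margins are then 1/3, so P_e = 6 × (1/3 × 1/3) = 2/3. P_o = (2/3)(1 − c), K = −c, and the pooled BI = (1 − c)/2. For MAG and SHM alone, P_e = 1/2, P_o = 1 − c, K = 1 − 2c, and BI = 1 − c.

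| Coil patients correct (c) | Pooled index, three arms | Index for MAG-SHM alone |
|---|---|---|
| 0.50 (pure guessing) | 0.25 | 0.50 |
| 0.75 | 0.125 | 0.25 |
| 1.00 | 0 | 0 |

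Under these assumptions, a pooled index of 0.25, halfway between random guessing and complete unblinding, would arise even if the coil pair were perfectly masked. A single pooled figure mixes an arm that cannot be masked with a pair that might be. The guesses are illustrative. Uncertain answers would change the values, and the documents give no expected guess distribution.

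**The case against.** The strongest reply is that most of this is already disclosed. Limitations names these modalities and the same route of bias, and the Discussion says that patient blinding was carried as far as was feasible and that the two modalities feel different. The blinding questionnaire lists ACU as an option, so it could reveal unmasking. This deserves credit, but it presents as a matter of degree something that is absent for two contrasts, and the unqualified sentence in Randomization and blinding is left as it is.

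A second reply is that the Discussion's sentence follows one stating that all arms receive the same rTMS. It may therefore mean only that the PC6 add-on is separated from that shared background. That is a fair partial reading. The sentence still speaks of specific effects and names acupuncture, so it needs clearer wording.

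A third reply is that the lead comparison is MAG against sham, which is not one of the two contrasts, and that the primary outcome is a scored cognitive test given by blinded assessors who take no part in treatment and follow a standardised manual. This stands, and it limits the weight of the point.

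Two stronger readings may tempt a reader. One is that the trial's main result is unblinded, or that assessor blinding fails; the documents support neither. The other is that only the 35 ACU patients of the 105 are affected. That count has no clear meaning, because coil patients also know that they are not in ACU. The proper unit is the contrast.

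**Conclusion.** The point holds as an inconsistency in the stated design. Participant blinding is claimed for the whole trial but is absent by construction for MAG-ACU and ACU-SHM, two of three contrasts. This rests on the interventions as described, with no sham needle or double dummy. The size of any expectation bias on MoCA or the secondary scales cannot be derived from the document.

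It would be wrong to infer that MAG-SHM is therefore securely masked. MAG is raised until the fingers visibly flex while the sham delivers nothing, and the protocol itself warns of functional unblinding there. Nor does the point show that a sham-needle arm was required. The choice of comparator can stand if the claims are fitted to it. Sample size and treatment are not affected.

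**What to change.** Reconcile Randomization and blinding, the Discussion and Limitations:

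1. State that participant masking is attempted only between MAG and SHM, and keep the existing caveat about functional unblinding in that pair.
2. State that contrasts involving ACU are open to participants, with blinded assessors and analysts.
3. In the Discussion, describe ACU contrasts as comparisons of treatment packages that include expectation, not as specific effects of acupuncture. In Limitations, say that participant masking is absent for these contrasts.
4. Report the blinding index by arm or for the MAG-SHM pair, and not only pooled over the three arms. The guesses already planned are enough for this.

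The cost is a change of wording and one additional tabulation, with no new data. The downside is weaker claims for the ACU contrasts.

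### A single James index pooled over three arms does not isolate MAG versus SHM masking, and 0.5 is not its chance value if needled patients recognise their arm

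*Protocol article*

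**What the plan says.** In the protocol article, Randomization and blinding, the blinding check follows the last treatment session: "All participants will be asked to guess their group allocation from four options: PC6 MAG, PC6 ACU, PC6 SHM, or uncertain". The summary measure is one index: "These responses will be used to calculate the James Blinding Index, which quantifies blinding success on a scale from 0 to 1". Its anchors are given as "where 1 indicates complete blinding" (everyone answers that they do not know), then "0 indicates complete unblinding (all correct), and 0.5 represents random guessing". No index by arm, and none for MAG against SHM, is named.

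The same section warns that "a higher risk of functional unblinding may exist between the MAG and SHM groups" and promises to take this into account in interpretation. Limitations adds that "blinding may be imperfect due to the distinct somatosensory experiences between acupuncture and magnetic stimulation".

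The ACU group section specifies real needling: "sterile disposable stainless-steel filiform needles (0.25 mm × 40 mm) will be inserted". Neither coil arm has a sham needle. In MAG, intensity is raised until slight finger flexion is seen. In SHM, frequency and intensity are zero and only the sound is matched.

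**The concern.** The masking that bears on the trial's main question is between MAG and SHM: the Discussion says the trial is to quantify what PC6 magnetic stimulation adds over sham. Between those arms masking can succeed or fail. Between ACU and the coil arms it can hardly succeed, because a patient who is needled daily for three weeks can be expected to know it.

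Putting all three arms into one index has two consequences. Correct ACU answers pull the value down whatever happens in the coil arms, so the 0.5 reference point no longer marks chance. And the James index raises its score for every 'uncertain' answer, so uncertainty in SHM can hide full recognition in MAG. The promise to consider the MAG/SHM risk does not repair this, since one pooled number cannot show which arm was unblinded or in which direction. The authors could then misjudge how far expectation might explain a MAG–SHM difference.

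**Working it through.** **Inputs from the protocol article.** Three arms of 35 (Sample size); four answer options and anchors 1 / 0 / 0.5 (Randomization and blinding).

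**Assumptions.** All ACU patients answer ACU. The article gives neither formula nor weights, so the standard form is used, with a correct guess weighted 0 and every wrong guess weighted equally (a constant weight cancels):

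James = [1 + P_DK + (1 − P_DK)·K] / 2, with K = (P_Do − P_De) / P_De.

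P_DK is the share answering 'uncertain'. P_Do and P_De are the observed and chance-expected shares of wrong answers among those who guess.

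**The stated anchors reproduce.**
- All uncertain: P_DK = 1, index 1.
- All correct: P_DK = 0, P_Do = 0, K = −1, index 0.
- Uniform guessing over three options in every arm: P_Do = P_De = 2/3, K = 0, index 0.5.

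So 0.5 is the chance value only if ACU patients guess at random too.

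**With ACU all correct.** Bang index per arm = (correct − incorrect) / n.

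| Case | P_DK | P_Do | P_De | K | Pooled James | Bang MAG / SHM |
|---|---|---|---|---|---|---|
| A. MAG and SHM both guess 50:50 between the coil arms | 0 | 1/3 | 2/3 | −0.50 | 0.250 | 0 / 0 |
| B. MAG all correct, SHM all uncertain | 1/3 | 0 | 1/2 | −1.00 | 0.333 | +1 / 0 |
| C. MAG all correct, SHM 50:50 | 0 | 1/6 | 2/3 | −0.75 | 0.125 | +1 / 0 |
| D. MAG and SHM all answer MAG | 0 | 1/3 | 2/3 | −0.50 | 0.250 | +1 / −1 |
| E. As A, but 20% uncertain in both coil arms | 0.133 | 0.308 | 0.663 | −0.536 | 0.335 | 0 / 0 |

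For example, B: [1 + 1/3 + (2/3)(−1)] / 2 = 0.333.

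- Chance guessing in the coil arms (A) gives half the stated chance value.
- B scores above A although every MAG patient knows the arm. A and D share one value although the answers differ.
- C falls below A, the right direction, so the misranking depends on 'uncertain' answers in SHM.
- If a share u of both coil arms is uncertain and the rest split 50:50, the pooled index is 0.250 at u = 0, 0.313 at 0.15, 0.335 at 0.20 and 0.467 at 0.50. B therefore exceeds equal masking only for u below about 0.20.

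**Weights.** With unequal weights for MAG–SHM confusions and confusions involving ACU, A ranged from 0.107 to 0.321 over the sets tried, while B stayed at 0.333. The ordering A < B held each time.

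**James index on MAG and SHM only.** Coin-flip guessing returns to 0.500. With MAG all correct and SHM 33 uncertain, 1 'MAG' and 1 'SHM': P_DK = 33/70 = 0.471, P_Do = 1/37 = 0.027, P_De = 107/1369 = 0.078, K = −0.654, index = [1 + 0.471 + 0.529(−0.654)] / 2 = 0.563, still above 0.500. In case B it is 0/0.

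**Precision of the Bang index.** At index 0 with everyone guessing and 33 analysed per arm: 1.96·√(1/33) = 0.34.

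**The case against.** A reader might infer that the pooled index rates an unblinded MAG arm above perfect masking. The documents do not support that in general. Their own top anchor is 1, for all answers 'do not know', and nothing can score higher. The misranking needs chance guessing with few 'uncertain' answers on one side and many 'uncertain' SHM answers on the other. It is a possible failure, not the expected behaviour.

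A reader might also infer that a low pooled value would be a false report of failed blinding. That goes too far as well. The protocol article describes participants in every arm as blinded. If ACU patients know their arm, a low value correctly shows that this claim failed for a third of the sample. It simply does not speak to MAG versus SHM.

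It can further be said that an article condenses, that nothing excludes a pairwise or by-arm report in the SAP, that the authors acknowledge imperfect blinding, and that no test or decision rule uses the index. All of this stands and limits the weight of the point. But the article does fix the index, the pool and the benchmark, and neither acknowledgement changes any of the three.

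**Conclusion.** The point holds in a limited form. On the plain reading of one index from all participants' answers, the planned measure does not isolate MAG/SHM masking, and 0.5 is the wrong reference once ACU patients recognise needling: chance guessing between the coil arms with no 'uncertain' answers gives 0.25. It can also misorder cases, with 0.33 for a fully unblinded MAG arm against that 0.25, but not against equal masking with about 20% or more 'uncertain' in both coil arms.

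This rests on ACU patients nearly all answering correctly, a strong inference from the needling procedure and consistent with Limitations, and on equal weights for the exact 0.25. The sample size and the primary MoCA test are untouched. At stake is how masking is reported and used to interpret MAG versus SHM, so this is a worthwhile, inexpensive improvement.

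**What to change.** Prespecify, in the protocol or SAP:

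- the Bang index with 95% CI, computed separately in MAG and in SHM from the same four-option answers, as the blinding measure;
- a table of all guesses by arm, with ACU descriptive. Any ACU guesses in the coil arms should be shown separately, because zero on the Bang index means random guessing only when guesses fall between MAG and SHM;
- that the 0.5 benchmark is not applied to the three-arm pool.

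Restricting the James index to MAG and SHM is not an adequate substitute, because it still credits 'uncertain' answers.

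The change costs about one sentence and needs no new question or data. The downside is two indices with wide intervals, about ±0.34 each at n = 33 if the index is 0 and all patients guess.
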